**8.2.2 Blood samples and laboratory variables**

Blood samples will be drawn from each patient on the following time-points:

- Baseline sample; between the inclusion (visit 0) and general anesthesia (visit1).
- Postoperatively, once daily on the first 7 postoperative days or until discharge (if earlier), respectively (visit 2-9).
- Additional blood samples will be drawn according to the decision of the investigator or other physicians. This refers to the case of technical problems during the initial visit or in case of loss of the baseline samples before surgery and/ or in case of clinical deviations, which require additional analyses. The following variables will be determined in each blood sample:
- Hematological variables: Erythrocytes, hemoglobin, hematocrit, leucocytes, and platelets.
- Renal variables: creatinine in serum, urea, cystatin C in serum for determination of GFR.
- Coagulation: Quick, INR, pTT
- Liver enzymes: ALT and AST
- Creatine kinase = CK
- Visit 10: Contacting of the family physician or attending urologist, to obtain the GFR and creatinine value, which was probably obtained during the clinical postoperative routine.

**8.3 Evaluation, documentation and analysis of the safety variables**

A specialized investigator will visit then patients daily until the 7^th^ postoperative day or until discharge (if earlier), respectively. An investigator is always available via telephone for events in-between these visits. All patient data will be documented in the CRF and evaluated by the investigator according to the SOP`s (standard operating procedures) of our hospital and the reference table. All data outside of range will be validated by the investigator and marked as clinically significant (cs) or not clinically significant (ncs). Each clinically significant value will be considered as an AE and documented in the adverse event section. The sponsor will be informed about the AEs.

8.4 Adverse events (AE)

An adverse event (AE) is any untoward medical occurrence in a patient or clinical investigation subject administered a pharmaceutical product and which does not necessarily have a causal relationship with this treatment. An adverse event (AE) can therefore be any unfavorable and unintended sign (including an abnormal laboratory finding), symptom, or disease temporally associated with the use of a medicinal (investigational) product, whether or not related to the medicinal (investigational) product. This can include diseases or symptoms, which occur or deteriorate after patient inclusion into the study (GCP-V §3 section 6). If the patients themselves or study personnel do not report AEs, they will be assessed by meticulous clinical examination, assessment of safety variables and a non-suggestive patient interview by the investigator. Furthermore, they will be documented thoroughly. If an investigator assumes an AE, he has to take all measures to make a diagnosis and the corresponding medical treatment. Patients will be observed and treated according to the medical need, until disappearing of symptoms, normalization of the laboratory variables and finding of a sufficient explanation for the observed event. Patients remain in-hospital until they meet the department and hospital standards for discharge. In addition, the investigator will evaluate, the dependence of the AE and the study treatment. The following will be documented in the CRF:

- Kind of AE (signs, symptoms or disease)
- Differentiation (serious/ not serious)
- Date of onset and end
- Intensity
- Causality to the investigational product
- Measures with regard to the study treatment or measures for recovery or improvement of patients` well-being
- Outcome of the event.

Intensity of the symptoms or the adverse event, respectively will be documented as follows:

- **Mild:** Perception of mild symptoms. Symptoms can be ignored easily or disappear, if the attention is diverted to other things.
- **Moderate:** Symptoms cause discomfort, but they are tolerable. They could not be ignored and compromise concentration.
- **Severe:** Severe symptoms, compromising the performance of usual activities.

Sponsor has to be informed about all AEs.

**8.5 Handling of serious adverse events (SAEs)**

- A serious adverse event (SAE) or serious adverse reaction (SAR) are defined as any adverse event or adverse reaction that:
- results in death (fatal) or
- is immediately life-threatening or
- results in persistent or significant disability/incapacity or
- requires or prolongs patient hospitalization or
- induces congenital anomaly/ birth defect.

In case of SAEs/ SARs, all measures described under 8.5 have to be taken and the SAEs/ SARs have to be documented in the CRF. In addition, the sponsor has to be informed immediately (<24h) by the investigator. Sponsor will inform the regulatory body (BfArM) in cases of suspected or confirmed causal relationship with the study treatment within the prescribed period (see 8.6). The investigator will provide a detailed written report after notification of the sponsor.

**8.6 Handling of suspected unexpected serious adverse reaction (SUSAR)**

An adverse reaction (AR) is any untoward and unintended response to an investigational medicinal product related to any dose administered. An unexpected adverse reaction (UAR) is a reaction with causality to the investigational product, which is not consistent with the applicable product information (e.g. summary of product characteristics). Diagnosis of a suspected unexpected serious adverse Reaction (SUSAR) has to be reported to the sponsor according to the guideline 2001/20/EG and the sponsor has to report it within 15 days to the respective Ethics Committee and the responsible authority (BfArM) (§13, section 2 GCP-V). This time-span is reduced to 7 days, if the suspected SUSAR has led to death or is immediately life threatening (§13, section 3 GCP-V).

**8.7 Review of the risk-benefit ratio**

Sponsor has to inform immediately, or within maximum 15 days the respective Ethics Committee and the responsible authority (BfArM) about each issue, which requires a new risk-benefit evaluation of the investigational product. This includes particularly:

- Case reports of expected serious reactions with unexpected outcome.
- Increasing incidence of expected clinically relevant serious reactions.
- Suspected cases of serious unexpected adverse reactions, after study termination.
- Events in connection with the study conduction or development of a investigational product, which could compromise the safety of the study participants.

**9 Statistics**

**9.1 Sample size**

Due to the lack of previous data, we can only calculate the sample size based on estimates. The aim of this pilot-study is to gather data about Xe, which could be used for a sample size calculation for a subsequent study. According to the literature and from own clinical experience we expect a maximum GFR decrease in the control group of 30% (54 ml min^-1^ 1.73 m^-2^). 10% less decrease in the Xe group, corresponding to 36 ml min^-1^ 1.73 m^-2^ in a healthy patient, have to be seen as a clinically significant difference. With a assumed scattering σ of about 80% of the difference of means δ (30 ml min^-1^ 1.73 m^-2^), a power of 1 - β = 80% and a two-sided significance of α = 5 %, we will need 23 patients per group, to see a significant effect. From our study experience we expect a dropout rate of 10%. Therefor, we will include 2 more patients per group. The total patient number in this pilot-study will be 25 patients per group. With this sample size we would be able to generate "positive signals" with 2-sided p-values below 20% for effects with a standardized difference of about δ /σ = 0.6 and a power of 80%. From clinical and economical reasons, a follow-up of this study idea would not be useful in case of significantly lower effects.

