**S2 Appendix. English translation of the German study protocol-**

**Background and Rationale**

**1.1 Background**

Renal cell carcinoma (RCC) is the third most common type of urological cancer in in Europe and the USA, with an increasing incidence due to incidental detection (with imaging techniques) of small mass tumors staged T1 [1-4]. A partial nephrectomy (PN) with preservation of nephrons is recommended in early-stage RCCs, under certain circumstances also in with stage T2 [5]. Notwithstanding the nephron-sparing effect of PN compared to radical nephrectomy, postoperative complications are common. This is due to the surgery-related ischemia during hilar clamping and indirect ischemia and reperfusion injury (IRI) involving tumor manipulation and resection itself [6]. Particularly impairment of renal function is common with a clinically significant glomerular filtration rate (GFR) decrease of 16-30% [6-8]. Beside limitations of clamping- and manipulation time, the use of cold ischemia for durations of more than 30 minutes ischemia, administration of mannitol, adequate hydration, avoidance of hypotension and blood loss, a postoperative GFR decline cannot fully be prevented [6-8]. After PN the GFR shows an initial nadir [8], followed by recovery to new reduced baseline levels. Evidence from clinical studies is limited [9], particularly in regard to the early postoperative maximum decrease of the GFR.

A therapeutic approach enhancing kidney-resilience to IRI would be of outstanding clinical relevance.

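### The inputs to the 5%-level sample-size calculation in Protocol 9.1 do not fit together, and 23 patients per group does not follow from them as written

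*Protocol*

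**What the plan says.** Section 9.1 of the Protocol makes two separate power statements.

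The first is at the conventional level. For the control group, "we expect a maximum GFR decrease in the control group of 30% (54 ml min^-1^ 1.73 m^-2"). For xenon it takes "10% less decrease in the Xe group, corresponding to 36 ml min^-1^ 1.73 m^-2^ in a healthy patient" as the clinically relevant contrast. It continues "With a assumed scattering σ of about 80% of the difference of means δ", with 30 ml/min/1.73 m² in brackets directly after δ, then "a power of 1 - β = 80" per cent and "a two-sided significance of α = 5" per cent, and concludes "we will need 23 patients per group". Two patients per group are added for a 10% dropout, giving 25.

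The second is a pilot criterion. With 25 per group the trial should produce a positive signal, defined as a two-sided p-value below 20%, "for effects with a standardized difference of about δ /σ = 0.6 and a power of 80" per cent. The section adds that effects clearly smaller than this would not justify a follow-up study.

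Section 9.3 sets the primary test at a two-sided 5% level.

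**The concern.** A reader cannot tell from the first statement what δ and σ are. The two decreases give one difference, the bracket gives another, and the stated ratio of σ to δ agrees with neither the bracket read as σ nor the final number. Depending on which figures are kept, the required size at two-sided 5% and 80% power runs from about 11 to 45 per group.

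The 80% power at 5% is the figure against which a non-significant primary test would be judged. If its basis cannot be recovered, p above 0.05 may be given more weight as evidence of no effect than the design supports. Section 9.1 also says the pilot is meant to inform the sample size of a later trial, so unclear planning values for δ and σ could be carried forward.

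**Working it through.** **Inputs, all from Protocol 9.1.** Control decrease 54 (30%). Xenon decrease 36, read as 20% (10 points less). Bracketed figure 30. σ about 0.8 × δ. Two-sided α 5%, power 80%, 23 per group before dropout and 25 after. Second statement: two-sided 20%, δ/σ = 0.6, power 80%.

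**Consistency of the inputs**
- Difference of means: 54 − 36 = 18. The bracket after δ says 30.
- If 30 is σ: 30/18 = 1.67, so σ is 167% of δ, not about 80%.
- Baseline implied by the decreases: 54/0.30 = 180 and 36/0.20 = 180. Section 9.1 does not state this baseline and describes the case as a healthy patient. It is three times the entry floor of 60 in the exclusion criteria.

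**Attempt to reproduce 23.** With d = δ/σ, the normal approximation per group is n = 2 × (1.960 + 0.842)² / d² = 15.70 / d². The t-test figures use the noncentral t distribution with 2n − 2 degrees of freedom and noncentrality d × √(n/2).

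| Reading | d | n, normal | n, t-test |
|---|---|---|---|
| σ = 0.8 δ, as written | 1.25 | 10.05 → 11 | 11.09 → 12 |
| 30/30 | 1.00 | 15.70 → 16 | 16.71 → 17 |
| ratio inverted, δ = 0.8 σ | 0.80 | 24.53 → 25 | 25.52 → 26 |
| 18/24 (σ = 0.8 × 30) | 0.75 | 27.91 → 28 | 28.90 → 29 |
| 18/30 | 0.60 | 43.60 → 44 | 44.59 → 45 |

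The ratio as written gives 11 to 12, about half of 23. It does so whatever value δ takes, because only the ratio enters the formula.

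**What the design delivers at two-sided 5% and 80% power (t-test)**
- 23 evaluable per group: d = 0.845, about 0.84.
- 25 evaluable per group: d = 0.809, about 0.81.

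**Check of the second statement (two-sided 20%, d = 0.6)**
- Normal approximation: n = 2 × (1.282 + 0.842)² / 0.36 = 25.04, in line with 25.
- t-test power: 79.5% with 25 per group and 76.9% with 23. The plan's 80% reproduces.

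**Power at the same d = 0.6 at the 5% level (t-test):** 51.2% with 23 per group and 54.7% with 25.

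**The case against.** The best defence is that the ratio was simply written the wrong way round. With δ about 80% of σ, d is 0.8. The normal approximation then gives 25, close to 23, and 23 per group has about 76–77% power. Dividing two figures printed in the paragraph, 30/36 = 0.833, even gives 15.70/0.694 = 22.6, so exactly 23 by normal approximation (24 by t-test). It would therefore be wrong to say that no reading gives 23. This stands, and it makes a wording error a plausible explanation. It does not rescue the text. The first route reverses the stated ratio. The second treats 36 as an SD, although the section labels it the xenon decrease.

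A reader might also infer that the plan claims 80% power for a standardized difference of 0.6 and really has only 51–55%. The document does not support that. It ties the 80% for 0.6 to two-sided p below 20%, and there it is right. Two effect sizes at two significance levels are not a contradiction. That 18/30 happens to equal 0.6 does not show that 18 and 30 were the planned δ and σ at 5%.

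The covariance analysis in 9.3 could add power through the baseline covariate. For 23 per group to reach 80% power at 5%, the correlation between baseline and decrease would have to be about 0.25–0.31 for d = 0.8, 0.42–0.45 for d = 0.75, or 0.69–0.70 for d = 0.6. The Protocol gives no correlation, so 23 cannot be derived this way.

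Finally, this is a pilot. The section admits that it rests on estimates and already has a 20% signal rule. That limits the harm of a result above 0.05, but it does not make the 5%-level calculation correct.

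**Conclusion.** The point holds for the 5%-level calculation only. As written, δ, σ and the figure 30 are mutually inconsistent, and 23 per group does not follow: the stated ratio needs 11 to 12, and the other readings tabulated need 17 to 45 by t-test. The stated size delivers 80% power at two-sided 5% for a standardized difference of about 0.81 (25 evaluable) to 0.84 (23 evaluable). The figures assume equal groups, a common SD, a two-sample t-test and no gain from baseline adjustment. The 20%-level statement is sound.

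Two further inferences go beyond the document. One is that a lower, more usual baseline GFR would cut power drastically. That requires shrinking δ with the baseline while holding the SD at 30; if the SD scales as well, the standardized difference does not change, and the Protocol gives no ground for scaling one without the other. The other is that a 30% control decline is an error because it sits at the top of the range in section 1.1 ("clinically significant glomerular filtration rate (GFR) decrease of 16-30" per cent). It is an optimistic expectation, but a stated one and inside the cited range.

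**What to change.** Keep 25 per group and rewrite the first half of 9.1:

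- State which δ, σ and baseline GFR were used, as one coherent set, with percentages and absolute values that agree. The authors must supply these; the document does not show that 18 and 30 were the intended pair.
- Replace the statement of 80% power at 5% with what the design gives: 80% power at two-sided 5% for a standardized difference of about 0.81 with 25 evaluable per group, or 0.84 with 23.
- For the plan's own standardized difference of 0.6, show both powers side by side: 51–55% at two-sided 5% and 77–80% at two-sided 20%, for 23 to 25 evaluable per group.
- Add one sentence saying that p above 0.05 in this pilot is not evidence of no effect.

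The cost is wording only, with no added patients. The downside is that the stated power at the conventional level becomes less favourable.

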**9.2 Patient selection for inclusion into the analysis**

All randomized patients will be included in the analysis.

**9.3 Statistical analysis**

All data will be collected descriptively according to the study protocol. After verification of the data in the SPSS-data base, they will be provided to the biometric institute (IMSIE, Cologne). A covariance-analysis will be used for analysis of the primary outcome GFR, by comparison of the data in the isoflurane- and Xe group for each time-point. The primary outcome, max. variation of the GFR, will be calculated according to 2.3.4. This primary outcome will be primary analyzed by covariance-analysis with the factor group and the covariate baseline value, with a 2-sided Mann- Whitney-Test with the level of 5%. Primary analysis will be performed according to the Intention-to-treat principle (missing values will be replaced by imputations, which will be pre-defined in a statistical analysis plan. This enables a conservative estimate of the effect). Secondary outcomes will be analyzed according to the per protocol analysis. Other variables will be analyzed descriptive and explorative with the common 2-sample T-test. Descriptive analysis for baseline and outcome variables will be performed with the usual measured values and parameters, graphics and tests (p-values) depending on the scale levels of the variables.

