**2.3 Secondary objectives/ secondary endpoints**

The following data will be assessed as secondary endpoints: Duration of direct manipulation-/ ischemia time during renal tumor resection; duration of anesthetic exposition before and after tumor resection; intraoperative blood loss, tumor size and histology; optional assessment of HIF 1 activation in healthy surrounding tissue; GFR time-course, determined by cystatin C assessment in serum; creatinine time-course within the first 7 days after PN; optional assessment of KIM-1 or NGAL in urine before and after tumor resection; urine output during surgery and on postoperative day 1-3; acute kidney injury with increasing AKIN-classification is already within 48h associated with increased mortality. This association was verified in several studies. A recent meta-analysis showed a doubled risk for mortality (RR= 2.4) for patients with AKIN I compared to patients without. Furthermore, it is increasing continuously from AKIN II to AKIN III (RR = 4.2 and RR = 6.4, respectively) and further on [35].

Macrophage migration-inhibiting factor (MIF) in serum will be assessed preoperatively, 5 minutes after termination of the tumor ground-treatment, directly postoperative in the PACU and after 24h. Additionally we will assess demographic data like age, height, BMI and anesthesia-related data (anesthetic-concentrations and amount of opioids and inspiratory oxygen-concentration) in this pilot-study. These data will be used to check the comparability of the two groups. According to GCP, safety data like vital patient data (oxygen saturation, blood pressure, heart rate) during anesthesia, laboratory data (blood cell count, coagulation data, urea, transaminases, creatine kinase) after surgery and all adverse events (AEs) und serious adverse events (SAEs) will be assessed in addition. After 3-6 months creatinine in serum and GFR should be determined for longer-term renal function course. This will be achieved by contacting of the familiar physician or urologist during the routine post-surgical care.

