**4.4 Patient exclusion criteria and procedure**

**4.4.1 Reasons for premature study-exclusion and termination of the investigational product administration**

- Patient safety has the first priority. A patient will be excluded before intervention, if an exclusion criterion appears after patient inclusion- but before intervention- (e.g. change of the surgical technique, acute patient deterioration, etc.). Patient data will receive a screening number and will be stored in a locker.
- A retrospectively noticed deviation from the inclusion or exclusion criteria (after the beginning of the intervention) will induce a study drop out. Depending on the time-point, the patient will receive a standard anesthesia and the data management will excluded the patient.
- Consent withdrawal: Patients can withdraw whenever they want. All collected data until the withdrawal time-point as well as the randomization group have to be filed. The patient has to be informed, that already collected data will be used further on.
- Severe adverse events (SAE) and suspected severe adverse reactions (SUSAR), which prohibit further study conduction.
- Adverse events (AE) and adverse reactions (AR), which seem to be hazardous for the physical and psychological health of the patients, as evaluated by the principle investigator.
- Technical difficulties and required modifications of the investigational product administration device.

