**7.1.3 Secondary outcomes**

The following secondary outcomes will be assessed in addition for the comparison of Xe anesthesia to isoflurane anesthesia:

- Measurement of the anesthesia and safety variables every 5 minutes and the determination of urine output at the end of surgery.
- Acute kidney failure determination according to the AKIN criteria, by measurement of the urine output every 6 hours until the second postoperative day, total urine output on the second postoperative day and determination of creatinine within the first 7 postoperative days or if earlier the day of discharge, respectively.
- Daily assessment of the safety data (creatinine, blood cell count, coagulation, urea in serum, transaminases and creatine kinase) until the 7^th^ postoperative day or if earlier the discharge day, respectively.
- Patients` vital data (blood pressure, heart rate, oxygen saturation) until the 7^th^ postoperative day or the discharge day (if earlier), respectively.
- Histological analysis with immunohistochemistry in paraffin sections and optional determination of HIF-1α in the tumor-free surrounding tissue via immunofluorescence staining.
- Determination of migration-inhibiting factor  (MIF) in serum.
- Determination of KIM-1 or NGAL in urine.
- Assessment of intraoperative blood loss.
- Assessment the anesthesia time until the beginning of the surgical ischemia (tumor resection time) and after the end of this surgical ischemia (defined by the termination of the tumor ground-treatment), until cessation of anesthesia. This will be assessed in collaboration of the investigator and the surgeons.
- Assessment of GFR and creatinine in serum after 3-6 months postoperative.

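### Per-protocol analysis of all secondary outcomes, AKI and safety data included, can omit patients excluded for safety events and contradicts section 9.2

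*Protocol*

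**What the plan says.** Protocol section 9.3 uses two analysis populations. For the primary endpoint: "Primary analysis will be performed according to the Intention-to-treat principle". For the rest: "Secondary outcomes will be analyzed according to the per protocol analysis". It makes no exception for safety data. Section 9.2 draws no such line: "All randomized patients will be included in the analysis".

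The secondary outcomes in section 7.1.3 include "Acute kidney failure determination according to the AKIN criteria, by measurement of the urine output every 6 hours until the second postoperative day" and "Daily assessment of the safety data (creatinine, blood cell count, coagulation, urea in serum, transaminases and creatine kinase", together with intraoperative safety variables and postoperative vital signs. AEs and SAEs are not in that list. Section 2.3, under its secondary endpoints heading, says that "all adverse events (AEs) und serious adverse events (SAEs) will be assessed in addition".

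Section 4.4.1 gives these among its reasons for exclusion: "Severe adverse events (SAE) and suspected severe adverse reactions (SUSAR), which prohibit further study conduction"; AEs and adverse reactions "which seem to be hazardous for the physical and psychological health of the patients", as judged by the principal investigator; and technical problems with the delivery device. Under section 4.4.2 such a patient leaves the study at once and, if still under study treatment, is switched to a standard anesthetic. Section 4.4.3 provides for data up to the point of exclusion, and section 4.4.4 replaces the patient.

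**The concern.** A per-protocol set is defined by what happens after randomization. Here some of the events that remove a patient are safety events, and the outcomes to be compared in the reduced set include safety and renal injury. If excluded patients differ from the others in AKI risk or laboratory course, or if exclusions are more frequent in one arm, the comparison no longer rests on randomization. The anesthetist who gives the treatment and sees intraoperative events is not blinded (section 3.2), so nothing in the design ensures that exclusions fall equally in the two arms.

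With 25 patients per group, two or three exclusions can move a proportion noticeably. The pilot is meant to supply data for planning a larger trial (sections 2.1 and 9.1), so distorted AKI and safety estimates would be carried forward. Separately, an analyst cannot follow sections 9.2 and 9.3 together as they stand.

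**Working it through.** The plan states no figure on this point, so the check is of the text, followed by an illustration with assumed counts.

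**Text, side by side**

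1. Section 9.3 assigns secondary outcomes to per protocol. Section 7.1.3 names AKI, safety laboratory data, intraoperative safety variables and vital signs as secondary outcomes, so the rule covers them. The sentence in 9.3 on other variables does not take them out.
2. Sections 4.4.1 and 4.4.2 exclude patients for certain SAEs, AEs and device problems. A patient taken off the allocated anesthetic and out of the study would not ordinarily count as treated per protocol.
3. Section 9.2 includes every randomized patient. Section 9.4 refers remaining missing data to intention to treat without limiting this to the primary outcome. Both conflict with step 1.
4. The document names no separate safety population.

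**Illustration**

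Inputs: 25 patients per group and 10% dropout (section 9.1). 10% of 25 is 2.5, so 2 or 3 patients per arm. The AKI count is an assumption, since the protocol gives none: 8 of 25 = 32.0%.

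Formula: with *x* patients excluded, *k* of them AKI cases, the per-protocol rate is (8 − *k*)/(25 − *x*).

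| Exclusions *x* | *k* | Rate | Shift from 32.0% |
|---|---|---|---|
| 3 | 0 | 8/22 = 36.4% | +4.4 points |
| 3 | 1 | 7/22 = 31.8% | −0.2 |
| 3 | 2 | 6/22 = 27.3% | −4.7 |
| 3 | 3 | 5/22 = 22.7% | −9.3 |
| 2 | 0 | 8/23 = 34.8% | +2.8 |
| 2 | 2 | 6/23 = 26.1% | −5.9 |

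If exclusion is unrelated to AKI, the expected *k* for *x* = 3 is 3 × 8/25 = 0.96, and the expected rate is (8 − 0.96)/22 = 32.0%, with no bias.

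With an assumed 5/25 (20.0%) and three exclusions, the range is 2/22 = 9.1% to 5/22 = 22.7%.

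Replacement under section 4.4.4 restores the number but not the composition. With three replacements at the assumed 32%, the 8/25 example runs from (5 + 0.96)/25 = 23.8% to (8 + 0.96)/25 = 35.8%.

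**The case against.** Several points on the other side are sound and limit the claim.

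- **The per-protocol set is undefined here.** A statistical analysis plan may define it. The omission of excluded patients follows from the ordinary meaning of the term together with section 4.4.2, not from an explicit sentence. This stands, but a definition elsewhere would not remove the conflict between 9.2 and 9.3, nor the choice of per protocol for AKI and safety.
- **Exclusion is narrow.** A reader might infer that all patients with AEs or SAEs are dropped. Section 4.4.1 excludes only for SAEs that preclude continuation and AEs judged hazardous. Most patients with events could remain, and data up to exclusion are kept.
- **Serious events need not vanish from the analysis.** A reader might infer that SAEs leading to exclusion would be counted as zero. The documents do not establish this. AEs and SAEs are absent from the 7.1.3 list, are documented and reported under section 8, and can be read as other variables to be described under 9.3.
- **AKI comes after treatment.** Anesthesia lasts about 3 hours (section 4.1) and AKIN status is determined on postoperative days 1 and 2, so AKI cannot itself stop the study anesthetic. Selection would mostly act through earlier events that may or may not be related to AKI. Section 4.4.2 does allow exclusion at any time, so a postoperative route remains open.
- **The direction is open.** A reader might infer that the results must look too safe, with a shift of about nine points. That is the extreme row, in which all three exclusions fall in one arm and all are AKI cases. Three of 25 is 12%, slightly above the protocol's 10% dropout.
- **The primary analysis is by intention to treat**, and the reasoning in 9.1 on whether to proceed rests on it. Secondary results are not stated to drive a decision.

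**Conclusion.** The point holds in a limited form. As written, section 9.3 sends AKI and the listed safety outcomes to an analysis set that, in its ordinary meaning, leaves out patients excluded for post-randomization safety events. It also contradicts section 9.2. The contradiction is certain from the text.

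The bias is possible rather than demonstrated. In the example with three exclusions in one arm it ranges from −9.3 to +4.4 percentage points, and it is zero in expectation if exclusion is unrelated to AKI. These figures rest on an assumed 8/25 AKI count and on excluded patients being omitted from the per-protocol set. The primary endpoint's stated population is not affected. What is at risk is the group comparison of AKI and safety data, not the recording or reporting of individual events.

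**What to change.** In section 9.3, replace the per-protocol sentence with three statements:

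- AKI and the other secondary efficacy outcomes are analysed in all randomized patients by allocated group.
- Safety laboratory data, vital signs and AEs/SAEs are analysed in all patients who received any study anesthetic.
- Per protocol is kept as a sensitivity analysis.

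Changing 9.3 alone is not enough. Reconcile it with 9.2, with 4.4.1 (where data management removes patients whose eligibility deviation is noticed after treatment has begun) and with 4.4.4, making clear that excluded and replaced patients remain in the analysis. Amend 4.4.3 so that outcome data already scheduled continue to be collected after exclusion unless consent is withdrawn. At present only data up to exclusion are secured, and section 4.4.5 merely recommends a final examination to those who withdraw.

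The cost is a few sentences of text and the continued follow-up of a small number of excluded patients, about 2 or 3 per arm at the protocol's own dropout rate. No new type of measurement is needed.
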